#### Efficacy

There are two co-primary outcome measures: the difference in mean Health
Assessment Questionnaire Disability Index (HAQ-DI) at 3 months and the
difference in modified Rodnan skin score (mRSS) at 3 months (compared to
baseline). The HAQ-DI is a self-administered questionnaire which has been
widely applied in studies of early dcSSc.^
21
^ It includes a visual analogue scale (VAS) for pain. It captures many
of the clinical features of early dcSSc expected to be improved by
corticosteroids. The mRSS^22,23^ is often the primary
outcome measure in trials of early dcSSc^24–26^ because it reflects
the overall disease process and is a predictor of outcome.^
27
^ Despite the short study duration (primary endpoint at 3 months),
having the mRSS as a co-primary outcome measure will allow comparisons
between PRedSS and other studies of early diffuse cutaneous disease. Both
HAQ-DI and mRSS are validated in SSc as per OMERACT (Outcome Measures in
Rheumatology) criteria.^
28
^

Secondary endpoints, most of which are self-administered questionnaires,
include the following:

a. The different VAS of the ‘Scleroderma HAQ’ (SHAQ)(21): in addition
to pain, these relate to Raynaud’s phenomenon, digital ulceration,
gastrointestinal and lung manifestations, and overall disease.b. The 11-point Scleroderma Functional Index,^
29
^ which is a SSc-specific index of functional ability,
measuring mainly upper limb function.c. The Scleroderma Skin Patient Reported Outcome (SSPRO).^
30
^ This was added 10 months after recruitment had commenced,
because it only became available after the study had started.d. The 5-D Itch scale.^
31
^ Itch adversely affects quality of life in patients with SSc,^
32
^ and patients with dcSSc attending the user group meeting
which informed PRedSS considered itch as one of the most troublesome
symptoms.e. The Cochin Hand Function Scale,^
33
^ which has been used extensively in studies of SSc and which
associates with the mRSS.^
34
^f. The Functional Assessment of Chronic Illness Therapy (FACIT)
questionnaire. This quantifies fatigue^35,36^ which is a significant symptom in patients with SSc^
37
^ including in patients with early dcSSc.^
34
^g. The Hospital Anxiety and Depression (HADS)^
38
^ Questionnaire, which quantifies anxiety and depression and
which has been widely applied in patients with SSc.^39,40^h. A helplessness questionnaire. The five Rheumatology Attitudes
Index (RAI) helplessness items are extracted from a larger
helplessness scale, the RAI.^41,42^i. The Short-form 36 (SF-36v2^®^)^
43
^ and EuroQol-5D (EQ-5D)^
44
^ questionnaires, which measure health-related quality of life
(HRQOL).j. Patient global assessment.

Non-patient reported outcome measures are as follows:

k. Physician global assessment;l. Examination findings: tender and swollen joint count,^
45
^ number of tendon friction rubs and number of digital (finger)
ulcers.

We were concerned at the potential ‘questionnaire burden’ of the study, and
therefore patient representatives were asked to complete the questionnaires
before the final decision as to which ones to include was made. The opinion
was that all should be included, because the patients felt it was important
to gain as much information as possible from the study. Once finalised, the
questionnaire pack was sent to a small sample of patients to assess average
time taken. The questionnaires take approximately 15–25 min to complete,
which patients thought was feasible. The Composite Response Index in
Systemic Sclerosis (CRISS) index^
46
^ is not being included as a secondary outcome because it includes lung
function, which is not being assessed in this study.

#### Safety

The main safety endpoints are changes in blood pressure and in renal function
(serum creatinine, estimated glomerular filtration rate, urinary
protein/creatinine ratio) and any serious adverse events including
infections. Patients are given the option of a personal blood pressure
monitor and asked to check and record their blood pressure at home at least
twice weekly, with advice to report immediately any new symptoms (e.g. new
breathlessness or headache) which could denote a sudden rise in blood
pressure. This voluntary self-assessment is not related to any of the
outcome measures. A full blood count and blood glucose are also checked at
each visit.

### Statistical aspects

#### Sample size calculation

This was based on HAQ-DI and mRSS as co-primary endpoints and employed a
reduced 2-tail significance level of 2.5% for each. Sample size was first
calculated for a two-group t-test of mean values at 3 months and then
adjusted for the planned more efficient analysis of covariance (ANCOVA)
analysis via a multiplier (1 − r^2^) where r is the assumed
correlation between baseline and 3-month values.^
47
^ A standard deviation of the HAQ-DI of 0.9 was used (based on previous
studies^8,48^ and data from the Salford Royal Hospital SSc
database). The correlation between HAQ-DI scores at baseline and at 1-year
follow-up (calculated from the clinical database) was 0.6. On the basis that
we want to see a large difference in the group means at 3 months in order to
proceed with prednisolone as intervention for early dcSSc, we selected a
minimum clinically relevant difference of 0.6 points on the HAQ-DI. This
corresponds to ‘marked improvement’ in the study of Khanna et al.^
49
^ which compared change in the HAQ-DI to clinician assessment. An
overall sample size of 60 patients (30 per arm) then gives 82% power to
detect a 0.6 difference at a 2.5% significance level, assuming analysis is
performed by an ANCOVA adjusting for baseline scores. An analogous
calculation was performed for mRSS, again informed by Autologous Stem cell
Transplantation International Scleroderma (ASTIS)^
8
^ and the SSc clinical database. Assuming a standard deviation of 8.2,
together with a correlation between baseline and follow-up scores of 0.9, 60
patients would then provide 99% power to detect a difference of 5.5 points
on the mRSS at a 2.5% significance level. Acknowledging that this estimate
of the correlation is very high and may not be repeated in the trial, we
repeated the calculation assuming a more modest correlation of 0.6. Sixty
patients would then also provide 82% power to detect a difference of 5.5
points on the mRSS at a 2.5% significance level. We anticipate having to
recruit approximately 12 more patients to account for attrition.

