#### Statistical analysis

Primary analyses will be conducted on an intention-to-treat basis; withdrawn
patients will continue to complete visits and their measurements will be
included in the analysis. The two co-primary outcome measures (HAQ-DI and
mRSS) will each be analysed as continuous variates using a Mixed Model for
Repeated Measures (MMRM) to assess any differences between the treatment
arms. Each model will include the fixed categorical effects of treatment
(i.e. prednisolone and placebo), time point (i.e. 6 weeks, 3 months and
6 months), whether a patient is anti-topoisomerase positive, baseline scores
as well as the interactions of all fixed terms by time point. This will
ensure the effects are permitted to vary for each of the three time points.
The models will also be adjusted for any baseline characteristics found to
be predictive of missing outcome values. A general unstructured covariance
matrix will be used (six parameters). The models will be fitted using
REstricted Maximum Likelihood (REML) and will employ Kenward and Roger
degrees of freedom adjustment. The primary focus will be the contrast
(adjusted mean difference) between treatment arms at 3 months.

There are a large number of secondary outcomes (listed in Table 2), and
these will be analysed in an analogous manner to the co-primary outcomes.
These analyses will be exploratory in nature each employing an unadjusted
2-tail 5% significance level for the trial arm comparison at 3 months.

Further exploratory analyses will compare the trial arms for the HAQ-DI, mRSS
and other secondary outcomes at the other time points, that is, 6 weeks and
6 months, respectively. A single interim futility analysis is planned after
approximately 30 participants have 3-month outcome data with early stopping
only permitted for lack of benefit in both co-primary outcomes.

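### The only test level given for the two co-primary outcomes is a plain Bonferroni 2.5% each; Holm's procedure keeps the same 5% family-wise error and adds about 7 to 11 points of power to show both

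*Protocol article*

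**What the plan says.** The Sample size calculation section of the protocol article says of its calculation: "This was based on HAQ-DI and mRSS as co-primary endpoints". It applies a "reduced 2-tail significance level of 2.5% for each", and every power figure there is for a single outcome at that level. No power to show both outcomes is given.

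The Statistical analysis section makes the 3-month contrast from a repeated-measures model the primary focus for each outcome. It gives no test level, step-down rule or success criterion for the pair. The only level it states is an unadjusted 5% for the secondary outcomes. The interim futility rule treats the two primaries together: early stopping is "only permitted for lack of benefit in both co-primary outcomes".

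**The concern.** Dividing 5% equally between two outcomes is the correction for a trial in which a benefit on either outcome counts. The futility rule fits that reading, since the trial continues while either outcome still shows promise. For that purpose plain Bonferroni is dominated. Holm tests the smaller p-value at 2.5% and, if it is significant, the other at 5%. It rejects everything Bonferroni rejects, sometimes more, and has the same bound on the family-wise error.

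At stake is the second outcome. The objectives name both disability and skin score. Suppose one outcome is significant at 2.5% and the other has a p-value between 0.025 and 0.05. Fixed 2.5% levels would call the second negative, and 5% family-wise control does not require that. In a trial of 60 evaluable patients with slow recruitment, this is power that can be had without recruiting anyone.

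**Working it through.** **Inputs (Sample size calculation section).**
- HAQ-DI: "A standard deviation of the HAQ-DI of 0.9 was used"; the correlation between baseline and 1-year "follow-up (calculated from the clinical database) was 0.6"; a "minimum clinically relevant difference of 0.6 points on the HAQ-DI".
- mRSS: SD 8.2, difference 5.5, baseline correlation r = 0.9 and, as a more cautious alternative, 0.6.
- 30 per arm, two-sided 2.5%, variance reduced in the ANCOVA "analysis via a multiplier (1 − r^2^) where r is the assumed" correlation between baseline and 3 months.
- Assumed, because the article does not give it: the correlation ρ between the two test statistics, taken from 0 to 0.9.

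**Step 1: reproduce the stated power.** SE = SD × √(1 − r²) × √(2/30); noncentrality = difference / SE; t distribution with 57 df. The two-sided critical values are 2.302 at 2.5% and 2.002 at 5%.

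| Outcome | Residual SD | SE | Noncentrality | Power at 2.5% | Power at 5% | Stated (2.5%) |
|---|---|---|---|---|---|---|
| HAQ-DI, r = 0.6 | 0.9 × 0.8 = 0.72 | 0.186 | 0.6/0.186 = 3.23 | 82.0% | 88.7% | 82% |
| mRSS, r = 0.6 | 8.2 × 0.8 = 6.56 | 1.694 | 5.5/1.694 = 3.25 | 82.5% | 89.1% | 82% |
| mRSS, r = 0.9 | 8.2 × √0.19 = 3.574 | 0.923 | 5.5/0.923 = 5.96 | 99.98% | >99.99% | 99% |

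The plan's figures reproduce.

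**Step 2: power to show both, by hand at ρ = 0 and mRSS r = 0.6.**
- Bonferroni needs both p ≤ 0.025: 0.8198 × 0.8248 = 0.676.
- Holm needs the smaller p ≤ 0.025 and the larger p ≤ 0.05. That is the chance that both are ≤ 0.05, less the chance that both fall between 0.025 and 0.05: 0.8874 × 0.8910 − (0.8874 − 0.8198) × (0.8910 − 0.8248) = 0.7907 − 0.0045 = 0.786.
- Gain: 11.0 points.

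**Step 3: other values of ρ, by simulation (1,000,000 draws or more per row).**

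| mRSS r | ρ | Bonferroni, both | Holm, both | Gain (points) |
|---|---|---|---|---|
| 0.6 | 0 | 67.6% | 78.6% | 11.0 |
| 0.6 | 0.3 | 69.8% | 79.7% | 9.9 |
| 0.6 | 0.5 | 71.6% | 80.8% | 9.2 |
| 0.6 | 0.7 | 73.8% | 82.1% | 8.3 |
| 0.6 | 0.8 | 75.1% | 82.8% | 7.7 |
| 0.6 | 0.9 | 76.7% | 83.6% | 6.9 |
| 0.9 | any, 0 to 0.9 | about 82.0% | about 88.7% | about 6.8 |

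With r = 0.9 the mRSS test almost always succeeds. Holm then tests HAQ-DI at 5% nearly every time, so the gain is the step from 82.0% to 88.7% in the HAQ-DI row of Step 1.

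**Step 4: what does not change.** Both rules start by comparing the smaller p-value with 2.5%, so the chance of showing at least one outcome is identical. With mRSS r = 0.6 it is 1 − (1 − 0.8198) × (1 − 0.8248) = 96.8% at ρ = 0, and by simulation 92.9% at ρ = 0.5. The sample size is therefore unaffected.

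**Step 5: error control.** With both null hypotheses true, Holm errs only if the smaller p-value is at most 0.025. At ρ = 0 that is 1 − 0.975² = 4.9%; the simulated rate at ρ = 0.8 is 4.0%. With one null hypothesis true, that hypothesis is never tested above 5%. The bound holds under any dependence.

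**The case against.** **The article does not say that the final tests are at 2.5%.** The level stands in the sample size text, and sizing at 2.5% is compatible with a Holm analysis, whose first step uses 2.5%. The final rule may be in an analysis plan that was not available. This stands: plain Bonferroni in the final analysis is an inference. It is a reasonable one, because 2.5% is the only level attached to the primary outcomes anywhere in the article.

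**Nothing stated is wrong.** This also stands. A reader might infer that the split is an error or that the trial is underpowered as sized. The article supports neither: Bonferroni is valid, and the single-outcome powers are correct for their inputs.

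**Showing both is not the stated success criterion.** A reader might take the term co-primary to mean that both outcomes must succeed, and conclude that no split was needed. No passage requires both, and the split and the futility rule point the other way. The joint power measures how much a positive trial can claim; it does not measure the chance of a positive trial.

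**A gain of 8 to 11 points is tempting to quote.** It holds only for mRSS r = 0.6 with ρ up to about 0.75. The article gives r = 0.9 first, where the gain is about 6.8 points, although it doubts that value itself.

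**The stakes are modest.** With r = 0.6, a p-value between 0.025 and 0.05 corresponds to an observed HAQ-DI difference of about 0.37 to 0.43 (0.186 × 2.002 to 0.186 × 2.302) or an mRSS difference of about 3.4 to 3.9. Both lie below the 0.6 and 5.5 used for sizing, and the estimates would be reported either way. This limits the importance of the point, but it gives no reason to prefer the rule that rejects less.

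**Conclusion.** The point holds as a missed efficiency. Tested at a fixed 2.5% each, the two outcomes are handled validly, but by a rule that Holm dominates. Under the plan's own inputs with 30 evaluable patients per arm, Holm adds about 7 to 11 points to the chance of showing both. The range covers both mRSS correlations in the article and an assumed between-outcome correlation of 0 to 0.9. The benefit is confined to claiming the second outcome once the first is significant. The conclusion presumes that the sizing level is also the final test level.

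**What to change.** Before any unblinded analysis, state that the 3-month treatment contrasts for HAQ-DI and mRSS are tested by Holm's procedure at two-sided 5% overall: the smaller p-value at 2.5% and, if it is significant, the other at 5%. Say in the same place that benefit on either outcome counts as a positive result, if that is what the sponsor intends. Keep the 2.5% sample size text as the conservative power for a single outcome.

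The cost is a sentence or two and no patients. The one drawback is that simultaneous confidence intervals consistent with Holm are less simple than 97.5% intervals; the 97.5% intervals can still be reported alongside the tests. If the analysis plan already contains a step-down rule, the sponsor need only confirm it.

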#### Statistical analysis

Primary analyses will be conducted on an intention-to-treat basis; withdrawn
patients will continue to complete visits and their measurements will be
included in the analysis. The two co-primary outcome measures (HAQ-DI and
mRSS) will each be analysed as continuous variates using a Mixed Model for
Repeated Measures (MMRM) to assess any differences between the treatment
arms. Each model will include the fixed categorical effects of treatment
(i.e. prednisolone and placebo), time point (i.e. 6 weeks, 3 months and
6 months), whether a patient is anti-topoisomerase positive, baseline scores
as well as the interactions of all fixed terms by time point. This will
ensure the effects are permitted to vary for each of the three time points.
The models will also be adjusted for any baseline characteristics found to
be predictive of missing outcome values. A general unstructured covariance
matrix will be used (six parameters). The models will be fitted using
REstricted Maximum Likelihood (REML) and will employ Kenward and Roger
degrees of freedom adjustment. The primary focus will be the contrast
(adjusted mean difference) between treatment arms at 3 months.

There are a large number of secondary outcomes (listed in Table 2), and
these will be analysed in an analogous manner to the co-primary outcomes.
These analyses will be exploratory in nature each employing an unadjusted
2-tail 5% significance level for the trial arm comparison at 3 months.

Further exploratory analyses will compare the trial arms for the HAQ-DI, mRSS
and other secondary outcomes at the other time points, that is, 6 weeks and
6 months, respectively. A single interim futility analysis is planned after
approximately 30 participants have 3-month outcome data with early stopping
only permitted for lack of benefit in both co-primary outcomes.

### Study setting

PRedSS is an initiative of the UK Scleroderma Study Group and will recruit from
16 centres in the United Kingdom. The initial plan was for 13 centres to recruit
72 patients over a 3-year period, but because of slow recruitment 3 new centres
have been added.

## Results

Recruitment began at one centre in December 2017, with a second centre opening in
March 2018. The first 12 centres opened by July 2019 and the 14th in January 2020:
opening the final two centres is currently on hold with the Covid-19 pandemic.
Opening centres took longer than planned but with over 12 centres open by the end of
2019 the study was recruiting as per the planned trajectory. To date, 25 patients
have been recruited.

### Covid-19 impact

On 23/3/2020, the decision was taken to break the code for the 11 patients
currently on trial treatment, as it was felt inappropriate for patients and
their clinicians to remain blinded to which patients were receiving prednisolone
treatment during the pandemic. This was against the background of the British
Society for Rheumatology recommending that patients on both immunosuppressant
therapy and prednisolone should be ‘social shielding’ as per National Health
Service England guidance. Given that 10 of the 11 patients were on either
mycophenolate mofetil or methotrexate, it was therefore considered untenable to
maintain the double-blind. All 11 patients remained on trial on an open-label
basis. Recruitment was suspended until deemed safe to re-open. Ethics approval
has been obtained to convert PRedSS to a randomised open-label study, which is
now a preferable approach given that ongoing concerns regarding Covid-19 would
often make it difficult to maintain the double-blind.

## Discussion

PRedSS seeks to answer a key question for patients with early dcSSc and their
clinicians – should corticosteroids be prescribed or not? If the answer is ‘yes’,
then the pathway to impact will be immediate as prednisolone is a low-cost drug with
which rheumatologists are very familiar.

Since PRedSS was opened, there have been no other studies reported specifically
examining the use of corticosteroids in early dcSSc, although a study of high dose
methylprednisolone in very early SSc (without skin involvement) (ClinicalTrials.gov
Identifier: NCT03059979) is currently underway.^
50
^ In the recently reported North America study of autologous stem cell transplantation,^
9
^ only one of 34 patients randomised to the transplantation regimen, which
included high dose corticosteroids (including six doses of intravenous
methylprednisolone 1 mg/kg) developed scleroderma renal crisis. While this does not
prove that corticosteroids are ‘safe’, it does lend some tentative support to our
viewpoint that they may not be so nephrotoxic as to deprive patients with early
dcSSc of the possibility of substantial symptomatic improvement, thus providing
further rationale for PRedSS.
